### Challenges with the intervention

Behaviour staging using the principles of the transtheoretical model has not been considered in many lifestyle intervention trials [29]. This in turn may have had impact on the long-term sustainability of changes that were observed. Previous lifestyle trials have also not consistently standardized the measurement or prescription of physical activity or dietary behavior [27,30-34]. Further, there has also been a lack of matching of physical activity to other lifestyle habits, such as dietary intake. Finally, whether the observed changes in behaviour and clinical outcomes are related to changes in basic physiological mechanisms that control health is also essential to understanding the impact of these interventions on the pathophysiology of hypertension and T2D.

In this setting of an epidemic of cardiovascular disease and poor lifestyle, the overall aim of the Staged Nutrition and Activity Counseling trial (SNAC) is to determine the blood pressure and blood glucose lowering effects of a matched or scaled physical activity and dietary lifestyle intervention among persons with high normal blood pressure and/or impaired glucose tolerance. Further, as most of these patients are seen in family practice, and given the key role family physicians may provide in achieving and sustaining lifestyle change, the intervention will be delivered compared to the usual care of family practice lifestyle management. Finally, few studies have suggested that lifestyle interventions (primarily single interventions) can improve physiological determinants of cardiovascular function and health [35,36]. Whether this is similar in a large primary care intervention with two simultaneous lifestyle interventions is unknown. It is anticipated that the results of SNAC will provide scientific rationale and guidance for the implementation of this important lifestyle intervention program designed to prevent hypertension and T2D among those at risk for cardiovascular disease.

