### Primary and Secondary Outcome Measures

#### Primary Outcome Measures

a) clinical - clinic blood pressure with an automated BP device BPTRU™; fasting glucose, b) physical fitness - predicted VO_2 max _using STEP test and measured VO_2 max _using a modified Balke exercise treadmill protocol; BMI, c) physiological measures: brachial and carotid artery endothelial flow-mediated dilation and function.

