#### Secondary Outcome Measures

a) clinical - 24-hour ambulatory blood pressure; 2-hour glucose tolerance testing, hemoglobin A1C, microalbumin; waist circumference, calorie counts, b) behavioural measures - stage of change, self efficacy for diet and physical activity change, quality of life (SF36), barriers and benefits scales, c) physiological measures - waist circumference, calorie counts, dietary composition, cardiac function (echocardiographic determination of systolic and diastolic function, and left ventricular wall dimensions and volume), vascular geometry and elastic properties of the carotid and brachial arteries, muscle sympathetic and nerve activity discharge patterns at rest and a response to lower body negative pressure. Blood chemistry included blood lipid profiles homocystine, serum insulin, rennin, aldosterone, cortisol, C-reactive protein (CRP), markers of endothelial function including vascular adhesion molecule (VCAM) and intracellular cell adhesion molecule 1 (ICAM-1), urinary catecholamines, and serum free fatty acid composition.

Effects dependent on demographic subgroups will be defined by age, gender, and practice setting. Since previous trials have suggested that lifestyle interventions achieve their greatest effects early on, and that effects tended to diminish over time, we will evaluate the durability of these effects to 12 months and then for a further 12 months thereafter to determine the intervention rate of decay.

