### Sample Size and Data Analysis

#### Sample Size

Data from a previous "feeding" trials including the DASH trial have estimated a standard deviation change in systolic blood pressure after the intervention was between 5.32 and 5.92 mmHg providing a 90% power [24]. In terms of change and blood glucose levels, 0.1 to 0.3 mmol. reduction are considered important in differentiation of the risk for the development of T2D [4]. For physiological outcomes' sample size estimate, we chose a mean difference between groups of 0.25 mm standard deviation as appropriate for change in vascular dimension. Previous work in our laboratory support the ability to detect the 2 mm difference in vessel diameter with a standard deviation of .025 mm following a similar lifestyle intervention. Hence, we required at least 10 subjects per group (two-tailed t-test, p < 0.025, power = 0.8). Assuming an 80% success rate in achieving suitable recordings in two test sites and a drop out rate of approximately 20%, we will recruit 40 subjects per treatment arm to the high normal blood pressure and IGT groups.

Initially, we anticipated recruiting about 5-10 patients per practice using a cluster design. To allow for the effect of this clustering we used an interpractice correlation coefficient (ICC) of 0.025. We felt this would be a conservative upper limit for the ICC on the basis of previous work in primary care. The inflation factor was therefore calculated to be 1+0.025 (10 minus 1) = 1.05. This figure gives a required number of patients per treatment arm of approximately 90 equivalent to 10 practices recruiting about 10 patients each.

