However, there is some theoretical loss of power from using variable cluster sizes. This is negligible in the current study of approximately 50 patients per treatment arm. Hence, our allocation method of 10 patients per practice was designed to avoid this possibility. Statistical analysis will include differences among the subjects' characteristics in clinical, behaivoural, and physiological outcome measures using analysis of variance (ANOVA). Interactions and/or a specific age, gender, or clinical variable differences will be examined using Tukey's post hoc analyses. If a group difference in a potentially confounding variable is observed at limit differences in a key outcome, analysis of covariance (ANCOVA) will be performed with the potentially confounding variable serving as the covariant. Relations of interest will be initially identified by univariate correlation analysis. Independent correlations among the dependent variables will be determined using partial correlation analyses and/or conventional multivariate step-wise regression analysis. In all cases, probability levels will be p < 0.05.

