## Discussion

The health benefits and implications of the SNAC lifestyle intervention could be substantial. In patients with a high risk for hypertension and T2D, each component of the SNAC intervention, including increasing physical activity and alteration of dietary intake, have been shown to reduce blood pressure and blood glucose in previous studies. However, a lack of implementation of these interventions using tailored primary care approaches has restricted the impact. The net effect of these small improvements in clinical variables can have quite significant effects on the prevention of hypertension and T2D, and hence cardiovascular risk [46]. Hence, the effects of the SNAC intervention on cardiovascular outcomes could be impressive.

It has been suggested that a population-wide approach of the DASH dietary pattern could reduce the incidence of coronary heart disease by 15% and stroke by 27% in U.S. adults just from BP reduction alone [47]. We suggest that the net effect of SNAC could be substantiately greater due to a combined lifestyle intervention but also, since the adherence and implementation to such a program could be greater through delivery in a family practice setting this seems even more likely than was observed in previous studies [48]. Further, we will identify the underlying behavioral and physiological determinants of these clinical changes. This will improve our understanding of the global improvement in patient cardiovascular risk.

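### Determinants of clinical change are selected by univariate screening, then partial correlation and/or stepwise regression, at an unadjusted p < 0.05, which cannot support a claim to have identified them

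*Protocol article*

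**What the plan says.** The last part of Sample Size and Data Analysis sets out a two-step search. Step one: "Relations of interest will be initially identified by univariate correlation analysis". Step two: "Independent correlations among the dependent variables will be determined using partial correlation analyses and/or conventional multivariate step-wise regression analysis". The closing rule covers both steps: "In all cases, probability levels will be p < 0.05". No shortlist of candidates, multiplicity adjustment, validation step or exploratory label accompanies this analysis.

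The use to be made of the result appears elsewhere. The Discussion says "we will identify the underlying behavioral and physiological determinants of these clinical changes". Challenges with the intervention, in describing gaps left by previous trials, says that "whether the observed changes in behaviour and clinical outcomes are related to changes in basic physiological mechanisms that control health is also essential" to understanding what such interventions do.

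The measures available as candidates are in the two outcome lists. The primary list includes "physiological measures: brachial and carotid artery endothelial flow-mediated dilation and function" beside clinic blood pressure, fasting glucose, fitness and BMI. The secondary list is long; its laboratory part alone begins "Blood chemistry included blood lipid profiles homocystine, serum insulin, rennin, aldosterone, cortisol, C-reactive protein (CRP), markers of endothelial function".

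**The concern.** A 5% test means what it says only when the variable tested was chosen without looking at the data. Here the variables reaching the second step are there because they already correlated with the outcome at 0.05. The second step therefore does not give a fresh 5% test of no relation, and the chance of a false declaration grows with the number of candidates screened.

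What is at stake is the mechanistic conclusion. If a search of this kind often returns an independent determinant when none exists, then finding one says little about whether a physiological or behavioural pathway is real. The Discussion's wording presents the result as established.

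**Working it through.** The article states no error rate for this search, only 0.05 per test, so there is no figure of its own to reproduce.

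**Inputs from the article**
- Level: 0.05 per test (Sample Size and Data Analysis).
- Sample size: 40 per arm (N = 80) on one reading of that section. On the other, "This figure gives a required number of patients per treatment arm of approximately 90" (N = 180).
- Intracluster correlation: 0.025 (same section).
- Pool of measures, by count: primary about 7 (clinic blood pressure, fasting glucose, predicted and measured VO2max, BMI, brachial and carotid flow-mediated dilation). Secondary about 6 clinical + 6 behavioural + 9 dietary, cardiac, vascular and sympathetic + 11 blood and urine = 32, with duplicated entries counted once. Total 7 + 32 = 39.

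**Assumptions, because the article is silent**
- Candidates entered: k = 10 to 40.
- Correlation among candidates: blocks of five with within-block correlation 0, 0.5 or 0.8; or one common correlation of 0.2 to 0.5.
- Global null: no candidate is related to the outcome.

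**Formula.** For k independent null candidates, P(at least one passes the screen) = 1 − 0.95^k. If stepwise entry uses the same 0.05, the best survivor always enters, so P(at least one declared) equals the chance that the screen passes anything. For k = 30: 1 − 0.95^30 = 0.785. The value first exceeds one half at k = 14: 1 − 0.95^14 = 0.512.

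**Simulation.** Screen at 0.05, then stepwise regression with entry and removal at 0.05; one response; 1,500 replicates per setting, so the Monte Carlo standard error is at most √(0.25/1500) = 0.013. Chance of at least one false determinant at N = 180:

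| k | 1 − 0.95^k | corr. 0 | corr. 0.5 | corr. 0.8 |
|---|---|---|---|---|
| 10 | 0.401 | 0.407 | 0.367 | 0.243 |
| 15 | 0.537 | 0.539 | 0.478 | 0.349 |
| 20 | 0.642 | 0.645 | 0.566 | 0.444 |
| 30 | 0.785 | 0.785 | 0.721 | 0.562 |
| 40 | 0.871 | 0.876 | 0.796 | 0.667 |

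**Sensitivity**
- N = 80 is nearly the same: k = 30 gives 0.771, 0.726 and 0.567; k = 10 gives 0.381, 0.347 and 0.233.
- One common correlation of 0.5 across all candidates, N = 180: k = 20, 30 and 40 give 0.415, 0.516 and 0.578.
- Clustering at 0.025 (k = 30, within-block 0.5, N = 180) gives 0.71, against 0.721 without it.
- Two responses, 20 independent candidates each: 1 − 0.95^40 = 0.87.

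Across all settings with one response, the range is 0.52 to 0.88 for 30 to 40 candidates and 0.23 to 0.65 for 10 to 20.

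**Reference for the fix.** Testing each of k independent candidates at 0.05/k gives 1 − (1 − 0.05/k)^k, about 0.049 for k = 10 to 40. For a list of three, 1 − (1 − 0.05/3)^3 = 0.049.

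**The case against.** The strongest reply is that the pool is assumed. The article lists outcome measures; it never says that 30 or more of them are screened against each clinical outcome, and its reference to relations of interest could mean a subset. Some listed items also re-measure the clinical outcomes. This stands, and it is why the size is given as a range. Setting aside clinic and ambulatory blood pressure, fasting and 2-hour glucose, and HbA1c still leaves about 39 − 5 = 34, so broad use would stay within 30 to 40. A short list would not, and the lower range then applies.

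Second, stepwise regression is only one permitted route; partial correlation is the other, and it was not simulated. True, but both start from the same univariate screen at 0.05, and in the stepwise case that screen alone sets the error rate.

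Third, this is a supportive analysis. The overall aim in Challenges with the intervention is to lower blood pressure and glucose, and the Abstract's primary analysis compares outcomes between arms. This stands and limits the weight of the point.

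A reader might also infer that the arms will be pooled, so that two outcomes both moved by the intervention correlate for that reason alone. The article does not say whether they are pooled, and partial correlation could condition on arm. The false-positive rate under pooling was 11 to 13% for assumed effects of 0.5 SD on both variables and 42 to 50% for 0.8 SD, but no such effects are stated in the article. This supports naming arm in the model as a precaution; it does not show an error.

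**Conclusion.** The point holds as a weakness in a method the article itself fixes, so it is not a complaint about detail left to an analysis plan. For one clinical outcome and no true relation, the chance of at least one false independent determinant is about 50 to 90% if 30 to 40 measures are screened, and about 25 to 65% with 10 to 20. Every setting tried is well above 5%. The figures rest on the assumed candidate counts and correlations and on the global null.

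A reader might go further and say that a positive mechanistic finding is near-certain whatever the truth. The documents do not support that. Only the global null was examined. With 10 candidates, or about 20 strongly correlated ones, the rate is below one half, and rates near 90% need many weakly correlated candidates or more than one response. Nor was any calculation made of how unstable the selected set would be or how inflated its coefficients.

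The between-arm comparison and the sample size do not depend on this step. The issue is minor to moderate: the selection rule and the strength of the Discussion's claim.

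**What to change.** Replace the univariate screen and stepwise selection with a short pre-specified list of hypothesised determinants for each clinical outcome. As an illustration, for clinic blood pressure the list might be change in brachial flow-mediated dilation, in measured VO2max and in BMI; the choice is the investigators'. Enter the whole list together in one model that includes arm, baseline value and practice, and apply Holm or false discovery rate control across the list. Label every other correlation exploratory. In the Discussion, replace the promise to identify determinants with a statement that associations with clinical change will be explored.

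This changes wording and analysis code only; no further data are needed. The price is fewer positive mechanistic claims and less freedom to search.

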**Methods/design:**

The Staged Nutrition and Activity Counseling (SNAC) study is a randomized clustered design clinical trial that will investigate the effectiveness and efficacy of a multi-component lifestyle intervention on cardiovascular disease risk factors and vascular function in patients at risk in primary care. Patients will be randomized by practice to either a standard of care lifestyle intervention or a behaviourally-based, matched prescriptive physical activity and diet change program. The primary goal is to increase physical activity and improve dietary intake according to Canada's Guides to Physical Activity Healthy Eating over 24 months. The primary intention to treat analysis will compare behavioral, physiological and metabolic outcomes at 6, 12 and 24 months post-randomization including estimation of incident hypertension and/or diabetes.

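### At least seven primary outcomes have no lead outcome, time point or success rule, all are tested at 0.05 against 0.025 in the vascular sizing, and the stated goal differs from the stated aim

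*Protocol article*

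**What the plan says.** - **Outcomes.** Primary Outcome Measures has three groups: clinical (clinic blood pressure, fasting glucose), fitness (predicted VO2max, measured VO2max, BMI) and physiological ("brachial and carotid artery endothelial flow-mediated dilation and function"). None is ranked above the others.
- **Time points.** The abstract has the primary intention-to-treat analysis compare outcomes at 6, 12 and 24 months, with none named as the lead.
- **Level in the analysis.** The analysis text ends: "In all cases, probability levels will be p < 0.05". Tukey's procedure is mentioned, but for interactions and for age, gender or clinical-variable differences, not for several outcomes or time points.
- **Level in the sample size.** For the vascular outcome: "Hence, we required at least 10 subjects per group (two-tailed t-test, p < 0.025, power = 0.8". The blood pressure and glucose statements give no level.
- **Objective.** The abstract says: "The primary goal is to increase physical activity and improve dietary intake". Challenges with the intervention gives the overall aim as to "determine the blood pressure and blood glucose lowering effects of a matched or scaled physical activity and dietary lifestyle intervention".
- **Where activity and diet are measured.** Calorie counts and dietary composition are secondary outcomes. Patients log activity (Schedule of visits), but activity behaviour is in neither outcome list.

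**The concern.** With several primary outcomes, a reader must know whether one success is enough or all are needed, and at which visit. The article does not say, yet it fixes 0.05 for every test. Under the natural reading that any primary result below 0.05 is a positive finding, the trial-level false-positive rate is well above 5%. Two further inconsistencies make the primary claim harder to pin down: the sample size and the analysis use different levels, and the article gives two different statements of what the trial is mainly for.

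**Working it through.** **1. The plan's own figure.** Ten per group at two-sided 0.025 and 80% power does not follow from the stated effect sizes. The normal approximation is n = 2(z₁₋α/₂ + z₀.₈)²/d², with 2(2.241 + 0.842)² ≈ 19.0.
- "we chose a mean difference between groups of 0.25 mm standard deviation as appropriate for change in vascular dimension", read as 0.25 SD: 19.0/0.0625 gives 305 per group. Read as 0.25 mm with an assumed SD of 0.25 mm: 20.
- "the ability to detect the 2 mm difference in vessel diameter with a standard deviation of .025 mm" is 80 SD, which needs 1 or 2.
- Ten per group corresponds to about 1.48 SD (t-test), which the article does not state.

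This is a separate matter. What is needed here is only that the level used was 0.025.

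**2. Count of primary outcomes.** Two clinical (blood pressure counted once) + three fitness + two physiological = 7. With systolic and diastolic separate, 8.

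**3. One time point, each test at 0.05, any one sufficient.**
- Independent: 1 − 0.95⁷ = 0.302. For eight, 1 − 0.95⁸ = 0.337.
- Correlated (assumed common correlation; multivariate normal simulation, 200,000 draws, seven outcomes):

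| Assumed correlation | At least one false positive |
|---|---|
| 0.3 | 27% |
| 0.5 | 23% |
| 0.7 | 18% |

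**4. If all three time points count.** 7 × 3 = 21 tests.
- Independent: 1 − 0.95²¹ = 0.659.
- With assumed correlations of 0.3 to 0.7 between outcomes and 0.5 to 0.9 between times: 28% to 56%.

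**5. Would 0.025 throughout suffice?** For two independent outcomes, yes: 1 − 0.975² = 0.049. For seven, no: 1 − 0.975⁷ = 0.162.

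**6. Direction of the level mismatch.** At 10 per group, the effect that gives 80% power at 0.025 (1.48 SD) gives 88% at 0.05. Testing at 0.05 what was sized at 0.025 therefore raises power.

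**7. Objective against outcomes.**

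| Statement | Content | Primary outcome that measures it |
|---|---|---|
| Abstract, primary goal | Activity and diet | None; diet is secondary, activity is in no list |
| Challenges with the intervention, overall aim | Blood pressure and glucose lowering | Clinic blood pressure, fasting glucose |

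**The case against.** **The analysis plan may settle this.** Success rules and multiplicity procedures are commonly left to a statistical analysis plan, which is not at hand. If success required all seven outcomes, the type I error would not inflate; power would fall instead. That is fair as far as the absence of a procedure goes. But the article states no such rule, and it is not silent on the level: it sets 0.05 for all cases. A later multiplicity plan would have to overrule that sentence.

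**Stronger readings that the document does not support:**
- *The trial would probably claim something by chance.* The 66% needs 21 independent tests, which is implausible when predicted and measured VO2max assess the same quantity. Under the assumed correlations the range is 28-56%. The count of three time points also rests on the abstract. Study Measurements does include 24 months, but Table 1 stops at week 52 and has no week 24 entry for the fitness and physiologic rows. Secondary Outcome Measures presents the second year as a study of durability.
- *The level mismatch undermines the power.* It does the reverse (step 6). The 0.025 is attached to the vascular calculation only, and it may be per-tail notation for 0.05, although the article does not say so.
- *The main claim has no outcome behind it.* The overall aim matches two primary outcomes, and the abstract's goal can be read as the behavioural target of the intervention. VO2max bears on activity indirectly, and diet is measured as a secondary outcome. What stands is that the two statements differ and that activity itself is not a named outcome.

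**Conclusion.** The point holds in limited form and should be corrected. The stated rule leaves the trial-level error uncontrolled across at least seven primary outcomes: 30% at one time point under independence and about 18-27% at assumed correlations of 0.7 to 0.3. These figures assume that any one outcome can carry the claim and that blood pressure counts once; the correlations are not in the document. The rate is higher if the three time points each count, but that extension is less firmly grounded. The 0.025 and 0.05 are a real inconsistency for the vascular outcome, without loss of power. The goal and the aim differ and need to be aligned.

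**What to change.** 1. Name one primary time point, for example 12 months, and treat the others as supportive.
2. Choose one of two rules:
   - **Holm** across the listed primary outcomes at overall two-sided 0.05, with the list closed (state whether systolic and diastolic pressure count separately). Holm controls the error at 5% whatever the correlations.
   - **Two confirmatory outcomes**, clinic systolic pressure and fasting glucose (the stated overall aim), each at two-sided 0.025, with the remaining outcomes supportive. The total is at most 0.05.
3. Replace the blanket 0.05 sentence with the chosen rule, and reconcile it with the 0.025 in the vascular calculation.
4. State one primary goal that matches the chosen outcomes, and list logged activity as a named outcome.
5. If glucose at 12 months is chosen, reconcile Table 1, which marks fasting glucose at baseline only, with Schedule of visits and Study Measurements, which describe repeat measurement.

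**Cost.** Mostly wording, plus a small correction to the visit schedule. Fewer outcomes can carry a confirmatory claim, and power per outcome falls. By normal approximation, a test with 80% power at 0.05 has Φ(1.960 + 0.842 − 2.241) = 71% at 0.025. At Holm's strictest step, 0.05/7 = 0.00714, it has Φ(1.960 + 0.842 − 2.690) = 54%; later Holm steps are less strict. Keeping 80% would need 1.21 or 1.59 times the sample size, so power for the chosen outcomes should be restated at the chosen level.
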